# Design of the Lifestyle Interventions for severe mentally ill Outpatients in the Netherlands (LION) trial; a cluster randomised controlled study of a multidimensional web tool intervention to improve cardiometabolic health in patients with severe mental illness

**DOI:** 10.1186/s12888-017-1265-7

**Published:** 2017-03-21

**Keywords:** Severe mental illness, Cardiometabolic health, Physical activity, Diet, Intervention, e-health, Web tool, Community-dwelling patients, Outpatients

## Abstract

**Background:**

The cardiometabolic health of persons with a severe mental illness (SMI) is alarming with obesity rates of 45-55% and diabetes type 2 rates of 10-15%. Unhealthy lifestyle behaviours play a large role in this. Despite the multidisciplinary guideline for SMI patients recommending to monitor and address patients’ lifestyle, most mental health care professionals have limited lifestyle-related knowledge and skills, and (lifestyle) treatment protocols are lacking. Evidence-based practical lifestyle tools may support both patients and staff in improving patients’ lifestyle. This paper describes the Lifestyle Interventions for severe mentally ill Outpatients in the Netherlands (LION) trial, to investigate whether a multidimensional lifestyle intervention using a web tool can be effective in improving cardiometabolic health in SMI patients.

**Methods/Design:**

The LION study is a 12-month pragmatic single-blind multi-site cluster randomised controlled trial. 21 Flexible Assertive Community Treatment (ACT) teams and eight sheltered living teams of five mental health organizations in the Netherlands are invited to participate. Per team, nurses are trained in motivational interviewing and use of the multidimensional web tool, covering lifestyle behaviour awareness, lifestyle knowledge, motivation and goal setting. Nurses coach patients to change their lifestyle using the web tool, motivational interviewing and stages-of-change techniques during biweekly sessions in a) assessing current lifestyle behaviour using the traffic light method (healthy behaviours colour green, unhealthy behaviours colour red), b) creating a lifestyle plan with maximum three attainable lifestyle goals and c) discussing the lifestyle plan regularly. The study population is SMI patients and statistical inference is on patient level using multilevel analyses. Primary outcome is waist circumference and other cardiometabolic risk factors after six and twelve months intervention, which are measured as part of routine outcome monitoring using standard protocols. Secondary outcomes include depressive and negative symptoms, cost-effectiveness, and barriers and facilitators in intervention implementation.

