### Aims of the trial

The aims of current pragmatic trial are to test whether a 12-month multidimensional lifestyle intervention, including aspects of increased awareness of own lifestyle and related risks, motivation, self-management, diet, exercise, and a supportive environment, is (cost-)effective in reducing cardiometabolic health and decreases depressive and negative symptoms. Also, barriers and facilitators in implementing the intervention on nurse and patient level will be explored.

The primary research question is:Is a 12-month multi-dimensional lifestyle approach including a web tool for SMI patients effective in improving or stabilising abdominal obesity (waist circumference) and other cardiometabolic risk factors in SMI patients after six and twelve months intervention compared to care as usual?

Secondary research questions are:2.Is a 12-month multi-dimensional lifestyle approach including a web tool for SMI patients effective in reducing depressive and negative symptoms in SMI patients after six and twelve months intervention compared to care as usual?3.Is a 12-month multi-dimensional lifestyle approach including a web tool for SMI patients aimed at improving or stabilising abdominal obesity (waist circumference) and other cardiometabolic risk factors in SMI patients after six and twelve months intervention compared to care as usual, cost-effective?4.What barriers and facilitators on nurse and patient level affect implementation of the 12-month multi-dimensional lifestyle approach?

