We hypothesize that this 12-months multi-dimensional lifestyle approach will improve cardiometabolic risk factors compared to patients who receive care as usual. Specifically, we expect the intervention to reduce waist circumference (WC), Body Mass Index (BMI) and Metabolic Syndrome Z-score (MS Z-score) after six and twelve months intervention because we expect that patients will try to increase their physical activity levels and improve their dietary habits. We expect that, through the intervention, patients will increase levels of physical activity and experience improvements in self-management skills and thereby improving self-efficacy [3, 14, 26], leading to a decrease in depressive [27] and negative symptoms [28] (i.e. lower depressive and negative symptoms scores). We hypothesize that the intervention will be cost-effective as costs will be relatively low (training of staff) while the physical and mental health of SMI patients will improve. Improvements in health, due to the increased self-management and increased exercise, might lead to less psychotropic drug use, such as antidepressants and anxiolytics [27, 28]. Finally, we will explore what barriers and facilitators on patient and nurse level have an influence on intervention implementation.

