### Participants

The study population consists of community-dwelling SMI patients and SMI patients living in sheltered facilities. Of this population, approximately 75% of the patients is diagnosed with a psychotic disorder, 15% with bipolar disorder and approximately 10% with complex personality disorders. In the North of the Netherlands, SMI patients are invited for annual Routine Outcome Monitoring screenings as part of standard care, consisting of a physical examination, a lab test and psychosocial measures. Patients are invited for the LION study when ROM screening outcomes indicate at least one of the following risk factors for metabolic syndrome: waist circumference > 88/102 cm (females/males); fasting glucose > 5.6 mmol/L or HbA1c > 5.7%; BMI > 25 kg/m^2^. Exclusion criteria are being pregnant, a BMI < 19 kg/m^2^, being primarily diagnosed with Korsakov syndrome or having a physical impairment which makes daily physical activity impossible. When patients are eligible for the study, they receive a detailed information letter from their case manager and, if willing to participate, sign informed consent.

The main objective of this trial is to detect an abdominal weight loss having public health significance. Previous work has indicated that 5-10 cm reduction in waist circumference (WC) is considered a realistic guideline with a high probability of health benefits [32]. For power calculations, we assumed 10% dropout rate. To include 250 participants, a 10% extra will be needed resulting in a total of 275 patients. Under these assumptions, and assuming an SD of 16.3 cm based on pilot data from this population, for two-sided 0.05-level tests of the null hypothesis, the study should provide approximately 80% power for detecting a difference of 5.8 cm in WC at 12 months between intervention and control groups. In addition, the study will have the same power to detect a reduction of 0.6 mmol/L in plasma glucose, given an SD of 1.7 mmol/L.

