### Statistical analysis

Variables will be presented as mean ± standard deviation (SD), and if not normally distributed as median [25th-75th percentiles], or N (%) for frequencies. Missing data are handled differently based on amount and type of missingness. If missing data can be well predicted by regression methods, multiple imputation will be considered. Otherwise, interpolation or replacement by study mean or median will be preferred over complete case analyses.

The primary outcome is the change in waist circumference (in cm) over time (from baseline to six and from baseline to twelve months) comparing the intervention group to the control group. This will be analysed with multilevel linear mixed models using teams as cluster. Analysis will be based on intention-to-treat principle. In per-protocol analyses, the intervention effect on cardiometabolic risk factors will be studied as described above, comparing participants with different degrees of intervention adherence to controls. Secondary study outcomes are analysed according to the same principles and techniques as the primary outcome. A priori sensitivity analyses are foreseen for participants’ age, gender and type of housing. In additional analyses, we will test whether the 12-months lifestyle intervention changes the level of motivation (stage-of-change) for changing diet of physical activity levels. An alpha of 0.05 is considered statistically significant.

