### Potential risks for bias

Some potential risks for bias might be expected. First, although patient selection bias should be minimal, it is still possible that it is difficult for nurses to include patients that are unmotivated to change their lifestyles in a lifestyle intervention study. Motivated patients are expected to be more easily included, leading towards patient selection bias based on the level of motivation. Second, because patients determine which lifestyle behaviours they wish to change, it is possible that they target other somatic health outcomes (e.g. dental health, sleeping patterns) than the primary study outcome waist circumferences and other cardiometabolic risk factors. In this case, stating that the intervention does not seem effective in reducing the primary outcome might be a biased conclusion when patients wished to change other health outcomes and might have been successful in addressing these changes. Third, although ROM is implemented on all sites, it is possible that not all sites have the capacity to conduct all measures, leading to missing values. In addition, ROM nurses cannot collect blood samples themselves but send patients an invitation to visit a (hospital) laboratory. Although ROM nurses convince and remind patients to do so, patients might be reluctant to go to the laboratory, also leading to possible missing values.

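### The primary outcome is defined in conflicting ways and no single contrast decides the trial, so the 5% error rate is not shown to be held

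*Protocol article*

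**What the plan says.** The protocol article describes the primary outcome or primary question in several places:

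- **Abstract, Methods/Design:** "Primary outcome is waist circumference and other cardiometabolic risk factors after six and twelve months intervention".
- **Aims of the trial, primary research question:** whether the intervention is "effective in improving or stabilising abdominal obesity (waist circumference) and other cardiometabolic risk factors in SMI patients after six and twelve months intervention".
- **Aims of the trial, hypotheses:** "we expect the intervention to reduce waist circumference (WC), Body Mass Index (BMI) and Metabolic Syndrome Z-score (MS Z-score) after six and twelve months".
- **Discussion, opening paragraph:** waist circumference together with other cardiometabolic risk factors, with no time point.
- **Potential risks for bias:** "the primary study outcome waist circumferences and other cardiometabolic risk factors".
- **Statistical analysis:** "The primary outcome is the change in waist circumference (in cm) over time (from baseline to six and from baseline to twelve months"), comparing the arms in a multilevel linear mixed model with teams as clusters.

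Two further statements bear on the decision rule. The Participants section gives about 80% power for a "difference of 5.8 cm in WC at 12 months between intervention and control groups" and then claims the same power for a 0.6 mmol/L reduction in plasma glucose, without a time point. The Statistical analysis section closes with one general rule: "An alpha of 0.05 is considered statistically significant".

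**The concern.** The definitions differ on two axes: which variables are primary, and at which visit.

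- **Variables.** Four places add an open set of risk factors to waist; the Statistical analysis section leaves them out. That section is not fully consistent itself. Its per-protocol sentence refers to the effect on cardiometabolic risk factors as already described, although the text before it describes only waist.
- **Visit.** Even the narrow definition contains two contrasts, six and twelve months, and nothing says which one decides. Only the power statement for waist points to 12 months.

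At stake is how a mixed result is read. Suppose waist differs at six months but not at twelve, or BMI differs and waist does not. The abstract's wording would allow a claim on the primary outcome in either case. The Statistical analysis wording would exclude the BMI result and leave the six-month result open. The power statement for waist would point to a null result in both cases. A choice made after the data are seen could raise the chance of a false primary claim above the nominal 5%.

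**Working it through.** **1. Reproducing the stated power**

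Inputs from the Participants section: 250 evaluable patients, SD 16.3 cm and difference 5.8 cm for waist, SD 1.7 and difference 0.6 mmol/L for glucose, two-sided alpha 0.05. Assumed: 1:1 allocation (125 per arm), since no ratio is stated. There is no design effect, in line with the article's own calculation.

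Power = Φ(δ / (SD × √(2/n)) − 1.96), with √(2/125) = 0.1265.

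- Waist: 5.8 / (16.3 × 0.1265) = 2.813; 2.813 − 1.960 = 0.853; power 80.3%.
- Glucose: 0.6 / (1.7 × 0.1265) = 2.790; 2.790 − 1.960 = 0.830; power 79.7%.

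Both agree with the stated figure of approximately 80%. Each calculation is for a single test at 0.05.

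**2. Error rate for the narrow definition (waist at six and twelve months)**

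Suppose there is no effect, each contrast is tested at two-sided 0.05, and either one counts as success. Then P(at least one) = 1 − P(|Z₁| < 1.96 and |Z₂| < 1.96), with Z₁ and Z₂ bivariate normal. With independence this is 1 − 0.95² = 9.75%. The correlation is not in the article, so a range is shown.

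| Correlation | At least one significant | Both significant |
|---|---|---|
| 0 | 9.75% | 0.25% |
| 0.5 | 9.1% | 0.9% |
| 0.8 | 7.8% | 2.2% |
| 0.9 | 7.0% | 3.0% |

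The last column is 0.05 + 0.05 minus the column before it. A rule requiring both visits stays below 5%. A single joint test at 0.05 would hold 5% by construction.

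**3. Error rate for a wider definition (illustration)**

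The hypotheses name three outcomes at two visits, so six tests. With independence this gives 1 − 0.95⁶ = 26.5%. With one common correlation between all six, by simulation: 20.8% at 0.5, 13.9% at 0.8 and 10.8% at 0.9. Both the count of six and the common correlation are assumptions, because the article never lists the other risk factors.

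**4. What the possible remedies do to power for 12-month waist**

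| Rule | Alpha for 12-month waist | Power with 250 | Evaluable patients for 80% |
|---|---|---|---|
| 12-month waist alone | 0.05 | 80.3% | 248 |
| Bonferroni, two waist contrasts | 0.025 | 71.6% | 302 |
| Bonferroni, six tests | 0.0083 | 56.9% | 384 |

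With 10% dropout, 302 evaluable patients means recruiting 302 / 0.9, or 336, against the 275 planned.

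**The case against.** The strongest reply has four parts.

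1. **This is a journal article, and multiplicity handling is usual analysis-plan content.** That is right as far as it goes: the absence of a testing order or an adjustment is not a finding by itself. The conflict between definitions is different. The article states the primary outcome repeatedly, and the statements disagree. An analysis plan that followed the Statistical analysis section would contradict the abstract and the primary research question.

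2. **The operative sections are narrower than the abstract.** The Statistical analysis section names waist, and the Participants section gives abdominal weight loss as the main objective. This limits the worst case under those sections to two waist contrasts, but it does not choose between the visits.

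3. **No success rule is stated.** A reader might infer that the 5% rate is definitely exceeded. The article does not support that. Change over time in a mixed model could be tested with one joint group-by-time test, or significance could be required at both visits; either would keep the rate at or below 5%. The alpha sentence is also a general one and does not say that each of several tests gets its own 0.05. What stands is that the rate is undetermined.

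4. **The larger error rates rest on assumptions.** A reader might take the open list of risk factors as licence for ten or more outcomes and arrive at a rate near one half. No such list is given, and the result depends heavily on the assumed count and correlations. The figures for six tests are illustrations for the same reason.

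A reader might also infer that power is stated only for 12-month waist. It is not: the same power is claimed for glucose. That adds to the ambiguity, because glucose is not in the waist-only definition.

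**Conclusion.** The point holds as an inconsistency in the definition of the primary outcome. The article gives waist plus unlisted risk factors in four places and waist alone in the Statistical analysis section. Both the abstract and the Statistical analysis section span two visits, and no contrast is named as decisive.

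The error-rate consequence is conditional. If any one significant primary test counts as success, the false-positive chance is about 7% to 9.75% under the narrow definition, for correlations from 0.9 down to 0. It is illustratively about 11% to 26% for the three hypothesised outcomes at both visits. The supported conclusion is therefore that control at 5% is not shown, rather than that it is lost.

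The stated power is not in dispute here: it reproduces for waist and for glucose, assuming 1:1 allocation and ignoring clustering as the article does.

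**What to change.** State one definition in the abstract, the primary research question, the Statistical analysis section, the opening of the Discussion and the section on potential risks for bias: the sole primary outcome is the between-arm difference in waist circumference at 12 months, tested at two-sided 0.05. This is the waist contrast on which the trial is sized, and it fits the stated main objective.

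Make six-month waist, BMI, metabolic syndrome Z-score, glucose and HbA1c, lipids and blood pressure secondary, reported with estimates and confidence intervals. Label the glucose power statement in the Participants section as secondary. If a formal claim on six-month waist is wanted, test it at 0.05 only after 12-month waist is significant; this fixed sequence costs no alpha.

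A joint test over both visits, or an alpha split, would also settle the matter. The Bonferroni split lowers power for 12-month waist to 71.6% with 250 patients, so the single contrast is the cheaper choice.

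The cost is wording only, with no added patients. The downside is that the six-month result and the other risk factors lose primary status, so a benefit seen only there could not be reported as the primary finding.

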**Discussion:**

Adequate health care should target both mental health and lifestyle behaviours in SMI patients. This trial contributes by studying a 12-month multidimensional lifestyle intervention as a potential evidence based (nursing) tool for targeting multiple lifestyle behaviours in SMI patients.

**Trial registration:**

Nederlands Trialregister NTR3765 (trialregister.nl; registered 21 December 2012).

## Background

The cardiometabolic health of persons with a severe mental illness (SMI), such as schizophrenia, other psychotic or bipolar disorders, is alarming with obesity rates of 45-55% and type 2 diabetes rates of 10-15% [1]. This is up to four times higher than in the general population of comparable age [1]. The increased risk in SMI patients is associated with their illness (negative and depressive symptoms lead to disinterests in and lower levels of autonomous motivation towards physical activity [2, 3]), their treatment (antipsychotic medication, inadequate somatic treatment) and lifestyle factors (e.g. lack of exercise, unhealthy diet, smoking) [1, 4].

In mental as well as in general health care, SMI patients may receive insufficient attention for their physical condition [5]. In the Netherlands, screening of somatic and mental health on a regular base is now obligatory for SMI patients according to the multidisciplinary guideline [6]. However, somatic screening results indicating increased risk of negative health outcomes are seldom translated into (adequate) treatment [7]. General practitioners working with these patients may lack knowledge of this specific population. On the other side, psychiatrists and other mental health professionals may lack knowledge and expertise in addressing lifestyle issues. Due to their knowledge on the SMI population and the frequent contacts, mental health nurses (MH nurse) are assumed to be the most adequate persons to address lifestyle behaviour change in SMI patients. Therefore, evidence-based lifestyle tools that provide MH nurses with knowledge, techniques and practical skills to stimulate patients in behaviour change are needed.

Lifestyle interventions have been shown to be effective in the reduction of body weight [8] and cardiometabolic risk factors such as waist circumference, triglycerides and fasting glucose in adults with SMI [9, 10]. However, the quality of studies on the effectiveness of lifestyle interventions in the SMI population is rather low, samples are small and results are inconsistent [10, 11], although one well-designed relatively large intervention RCT has recently been published [12]. Systematic reviews on lifestyle interventions in different populations indicate that, to be effective, a lifestyle intervention should contain at least three key components: exercise, diet and behavioural therapy [11]. Behavioural therapy strategies that enhance individual behavioural change include improving self-management skills such as tailoring information to the individual, identifying (lifestyle) areas for improvement, goal setting, making action plans, giving personalized feedback to reinforce new behaviours and using social and environmental strategies to support change [13, 14]. However, most of these techniques have a limited effect, and only work well for patients who are motivated [15]. An approach to deal with unmotivated patients or patients who are not ready to change yet, is the motivational interviewing (MI) approach of Miller and Rollnick [16] combined with the stages-of-change from the transtheoretical model of Prochaska and DiClemente [17]. MI is a patient-centred counselling approach that targets behaviour change by addressing intrinsic motivation. MI seems more effective than traditional methods in targeting lifestyle change [18]. It has been shown to be effective in improving weight status, Body Mass Index (BMI) and cholesterol levels of overweight and obese adults and of clients in a broad range of other domains [19, 20]. According to the stages-of-change from the transtheoretical model, patients’ level of motivation and self-efficacy to change is reflected in one of the five stages of change [21, 22]: the precontemplation, contemplation, preparation, action or maintenance stage, ranging from no intention to change till the motivation to maintain behaviour change. Treatment (or intervention) should adapt to a patient’s stage-of-change in order to increase intrinsic motivation for behaviour change [21]. A combination of action planning with feedback and a motivational stages-of-change approach is believed to be effective in behavioural change in SMI patients [23]. In addition, mental care is nowadays more rooted in the community and therefore more depending on SMI patients’ peers, families and environment. Therefore, peer and family support is considered an essential component for successful intervention implementation.

In the Lifestyle Interventions for severe mentally ill Outpatients in the Netherlands (LION) trial, we propose a patient-centred multidimensional intervention using a web tool consisting of several of the above described successful intervention components, e.g. raising awareness of own lifestyle behaviours, goal setting, addressing motivation to change, personalized feedback, integrating support of friends and family and searching for healthy lifestyle activities in local communities (e.g. local sport clubs). An advantage of the intervention is that the tool addresses patients’ level of motivation (stage-of-change) to change diet and physical activity levels and that nurses are trained in motivational interviewing. This combination makes the intervention suitable for patients who do not seem motivated to change their lifestyle, indicating the intervention is considered eligible for more or less every patient. Due to the feasible character of the intervention, this trial will aim for a large sample size (~N = 250). Another unique feature of this trial is the pragmatic character of the intervention. Often, lifestyle interventions are implemented by external staff in strictly controlled conditions, recruiting the most motivated patients [8, 24]. In regular care however, staff with different levels of expertise will need to implement the intervention with available resources (e.g. time, budget), a high workload with competing priorities, and working with patients who may be unmotivated [8, 13]. This trial will show outcomes with high external validity of a lifestyle intervention implemented in a real-world care setting.

The pilot study seems promising: after three months intervention, patients receiving the multidimensional lifestyle intervention (*N* = 20) lost on average three kilograms of body weight compared to care-as-usual (CAU) controls, performed more physical activity and rated their general well-being as better than patients receiving CAU (*N* = 20) [25]. Patients mentioned as enabling factors the role of nurses in stimulating a healthy lifestyle, and that more physical activity made them feel better, which enabled them to change other lifestyle factors as well. The intervention was well appreciated by patients and staff.

